## Abstract

**Background:**

Algorithm-based patient navigation is a key feature of the emergency and acute care reform being discussed in Germany. The software Structured Initial Medical Evaluation in Germany (SmED) is designed to assist in determining the appropriate time for medical complaints to be treated, as well as their most appropriate level of care. SmED is available in three different configurations, each of which is currently used in the German acute care sector and can be utilized by either a provider (SmED-Contact, SmED-Contact +) or a self-applicant (SmED-Patient). SmED-Patient is offered as a web-based self-assessment application that provides recommendations on the medical urgency and appropriate level of care for acute symptoms. This is the first study to explore and evaluate the accuracy, safety, utility and feasibility of using the self-assessment application SmED-Patient for self-referring patients and medical staff in the emergency department (ED) setting in Germany.

**Methods:**

The study uses a mixed methods approach, including a prospective, multicenter cohort study combined with retrospective expert review of SmED-Patient recommendations for all cases by an expert panel as well as focus groups and a microsimulation. Expert reviews assess SmED-Patient recommendations on patients’ treatment urgency and the appropriate level of care based on routine clinical data. Adult patients (≥ 18 years) who self-refer at two inner-city emergency departments in Berlin (Germany) and able to provide written informed consent will be invited to participate. Target number of patients is *n* = 150. The primary endpoint is the accuracy of SmED-Patient’s recommended level of care, measured as the agreement with the expert review for all cases. Secondary endpoints include safety, utility and feasibility of use. Data sources include primary data, routine clinical data, and qualitative data from focus groups and a microsimulation.

**Discussion:**

This study will provide insight into the accuracy, utility, safety and feasibility of using the self-assessment application SmED-Patient in the ED. By facilitating medical self-assessment for self-referring walk-in patients, SmED-Patient could contribute to re-directing patients to ambulatory care providers, improving the efficiency of ED operations and benefit providers’ as well as patients’ care experiences in the ED.

**Trial registration:**

German Clinical Trials Register: DRKS00036266. 25/02/2025.

**Supplementary Information:**

The online version contains supplementary material available at 10.1186/s13063-025-09101-4.

## Introduction

### Background and rationale {6a}

In contrast to a gatekeeper system, patients in non-gatekeeper systems, such as Germany, are under much greater pressure to make appropriate healthcare choices [see 1]. As a result, patients may not always present to the most appropriate provider. In Germany, around 45% of emergency department (ED) patients present without referral based on self-assessment of symptoms [2]. A recent study of routine clinical data collected in German EDs demonstrated that 33.2% of all analyzed ED presentations were retrospectively classified as “low acute” [3]. This suggests that some of these cases may not have required emergency care and could have been effectively managed at an alternative level of care. Even though these cases are unlikely to cause ED crowding, this patient group is especially affected by long waiting times in a crowded ED situation which negatively impacts patient and provider satisfaction and results in a higher number of patients left without being seen [4]. In addition, low acuity patients may not find the optimal care for their needs in EDs. In the German case, ED physicians can neither issue sick notes, nor prescribe reimbursable medication for Statutory Health Insurance (SHI) patients, and as in general, EDs do not provide long-term care (see [5]). ED interaction is also characterized by a particular lack of time, likely putting pressure on patients to communicate symptoms and receive advice on health issues [6]. In light of these considerations, the establishment of standards and tools for safe and effective patient navigation at appropriate levels of care is a desirable policy goal, and its use is increasingly supported by healthcare providers and policy actors [7–11]. However, there is currently no single endorsed algorithm-assisted decision support system for patient navigation in Germany, and evidence base on their accuracy, safety, utility and feasibility of use is still limited [12, 13].

The leading example of widespread pilot use of an algorithm-based patient navigation support system in Germany is the Structured Initial Medical Evaluation in Germany (SmED). SmED is a German configuration based on the validated assessment system SMASS (Swiss Medical Assessment System) [14]. Its configuration SmED-Contact is used by providers for telephone-based assessments as part of the on-call medical service of the Regional Association of SHI Physicians (available in Germany on 116117). The SmED-Contact + configuration is being piloted by providers with direct patient contact, such as ambulance services, outpatient practices and hospitals with integrated acute outpatient care [13]. Providers and policymakers alike expect the primary benefits of a generalized use of algorithm-based patient navigation to be efficient and safe patient allocation, contributing to improved cost-effectiveness and reducing the resource demands associated with emergency and acute care settings [12].

The current utilization, research, and debate surrounding algorithm-assisted patient navigation support systems primarily focus on the use by healthcare professionals. While the evidence base for these systems is growing [15], it is even more scarce for algorithm-assisted patient self-assessment and navigation in acute and emergency care settings. This finding is unexpected in light of the growing popularity of Symptom Assessment Applications (SAAs) among laypeople [16, 17] and their purported advantages for self-assessment and self-navigation, particularly in complex, non-gatekeeper systems.

Early studies suggest that the use of SAAs by laypersons to self-assess the urgency of symptoms is beneficial and produces more accurate results than unassisted self-assessments [18]. Further studies have shown that using a SAA as a triage tool in EDs can enhance safety [14], potentially improving operational efficiency. At the same time, further research has highlighted inconsistencies in urgency level assessments between healthcare providers and SAAs [19]. Notably, most existing studies focus primarily on patient safety, often relying on patient vignettes rather than real-world data [20].

While the emphasis on patient safety is crucial, it tends to overshadow other potential benefits of implementing SAAs in the ED. For instance, SAAs could support ED consultations by preparing patients for symptom-centered conversations, which may ultimately facilitate patient-provider interactions [21]; SAAs could also serve to bridge patients’ lack of health and system literacy, facilitating future decisions about healthcare utilization. In order to address these and the above research gaps and to integrate them into an overall research agenda, the present study examines the accuracy, safety, utility and feasibility of utilizing an algorithm-based symptom self-assessment application for self-presenting patients and their healthcare providers in the ED, conducting a prospective, multicentered, mixed-methods cohort trial. It uses SmED-Patient as another SmED configuration currently applied by the on-call medical service of the SHI Physician’s Association in Germany (available at https://www.116117.de/de/patienten-navi.php). This web-based tool for self-assessing the urgency of symptoms is comparable to other tools offered by international acute and emergency care providers (e.g., 111 online by the NHS, https://111.nhs.uk/). It is part of the SmED “system family,” using the same algorithm but is designed for lay use in the preclinical setting.

This is the first study to thoroughly evaluate the accuracy, safety, utility and feasibility of using SmED-Patient in the ED setting for both ED patients and providers in Germany.

### Objectives {7}

#### Primary objective

The primary objective of the study is to measure the accuracy of the SmED-Patient recommendation for the patient care level by analyzing its agreement with the recommendation of the expert panel for all cases (see Table 3).

#### Secondary objectives

To investigate SmED-Patient’s recommendation and symptom assessment compared to the retrospective symptom assessment of attending ED doctors and the utility of the SmED-Patient symptom short report in the ED for a sub-sample of *n* = 30–60 cases (*symptom assessment overlap and utility*).To investigate the agreement of recommendations between SmED-Patient and SmED Contact + (*SmED rating agreement*).To investigate the proportion of cases in which the SmED-Patient recommendation is assessed to be potentially patient endangering or inappropriate by experts (*safety and appropriateness*).To investigate SmED-Patient’s utility, including its comprehensibility, usability, response confidence, response time, satisfaction, trust and hypothetical compliance as well as preparedness for the medical consultation by patients, including subgroup analysis to explore aspects that influence patients’ assessment, e.g., health literacy, age (*patient utility*).To investigate the utility of SmED-Patient to providers in the ED setting, including practical utility of use and perceived benefits of a SmED-Patient implementation in the ED (*provider utility*).To investigate the proportion of disagreement between the patient self-assessment of urgency without decision-support and the SmED-Patient assessment of urgency (*patient urgency*).To investigate the feasibility of implementing SmED-Patient in the ED setting (*feasibility*).

### Trial design {8}

The study is a prospective, multicentre cohort study of adult self-referred patients in the ED to assess the accuracy of the SmED-Patient recommendation as compared to an expert panel (gold standard). A parallel mixed-methods approach is chosen to compare, integrate and validate the research results through triangulation for inclusion of different data sources, data methods and conceptual perspectives [22].

## Methods: participants, interventions and outcomes

### Study setting {9}

The study is a multicenter, ED-based trial with two study sites in Berlin, Germany. The study sites are the EDs of a large tertiary care hospital, representing an ED with standard care and an ED that integrated standard ED care with outpatient care (“fast track”) provided by an ED physician.

### Eligibility criteria {10}

The inclusion and exclusion criteria for the prospective, multicenter cohort study were selected in a manner that was as inclusive as possible in order to avoid any potential for selection bias. The criteria focus on patients who are potential users of a tool like SmED-Patient, reflecting the conditions under which such a tool might be used in the acute and emergency care context (e.g., low-acuity complaints). Inclusion and exclusion criteria for participation in the prospective cohort study are as follows:Inclusion criteriaAge ≥ 18 yearsSelf-referred walk-in presentation at one of the participating EDsAbility to perform the SmED-Patient assessment and the prospective survey (adequate German or English language skills, verbal communication possible, adequate cognition, etc.)Exclusion criteriaMinor ageMedical referral or medical transport to the EDInsufficient knowledge of the German or English language to understand the information about the study contents, provide consent and participate in the studyInsufficient cognitive status to understand the information about the study contents and to consent to the studyLegal guardianship (due to potential conflicts with time-sensitive study measures if the legal guardian is not present)Patients requiring immediate medical care (e.g., unstable, intubated patients)Prior medical contact with a physician in the ED

The inclusion and exclusion criteria were assessed through prescreening in in the ED’s digital documentation system (E.CARE ED) and through verbal interactions with patients by trained study personnel.

### Who will take informed consent? {26a}

Eligible patients will be asked to provide verbal and written informed consent by the study staff following ED triage. A copy of the signed informed consent form, approved by the Research Ethics Committee of the Charité – Universitätsmedizin Berlin, will be provided to the participant, as well as an information leaflet about the study, including information about data protection, participants’ rights and relevant contact information. Participants may withdraw from the study at any time without affecting their treatment. The informed consent process is conducted in accordance with the Declaration of Helsinki and complies with the EU General Data Protection Regulation (GDPR).

For patients who decline to participate in the study their reasons for not participating will be anonymously documented and results will be reported descriptively. This allows for insights into the selection bias of the study and the characterization of patient groups unsuitable for performing self-assessments of symptoms in the ED setting using SmED-Patient.

### Additional consent provisions for collection and use of participant data and biological specimens {26b}

Participants in the study measures of module 2 to 4, consisting of an expert panel, focus group interviews, a microsimulation and their evaluation (see Fig. 2) will give verbal and written informed consent. Participants will be offered a copy of the signed consent form and an information leaflet about the study measure. Both the informed consent forms and the information leaflets for each study measure have been approved by the Research Ethics Committee of the Charité—Universitätsmedizin Berlin.

Nurses will be asked to provide verbal informed consent for the pilot study of nurse assessment of urgency in the ED.

No biological samples will be taken that go beyond standard care.

## Interventions

### Explanation for the choice of comparators {6b}

This is an observational study that does not involve a clinical intervention. During the study, there will be no treatment intervention based on the recommendation of SmED-Patient or SmED-Contact +. ED treatment will follow usual routine care. As part of the study measures, the study provides a comparison and assessment of the overlap in results between two SmED configurations (SmED-Patient, SmED-Contact +) as well as an expert panel recommendation regarding appropriate care level.

### Intervention description {11a}

The software “Strukturierte medizinische Ersteinschätzung in Deutschland” (SmED) is designed to assist in determining the appropriate time to treat (see Table 1) as well as the most appropriate point of care (see Table 2). Tables 1 and 2 provide an overview of the urgency and care levels defined by the SmED manufacturer (manufacturer: in4medicine AG, Bern, Switzerland; Importer: Health Care Quality Systems [HCQS], Göttingen, Germany).

**Table 1 Tab1:** Level of urgency according to “time to treat” and corresponding treatment recommendations

Time to treat	Name	Recommended action
1	Emergency	CPR readiness. There is a potentially life-threatening condition. Medical treatment must be given now.
2	Immediately	Medical treatment does not allow any delay. Treatment should be given immediately.
3	Today	Medical treatment does not have to take place immediately. Medical treatment should take place within the next 24 h.
4	Later	Medical treatment is not urgent. If the symptoms do not subside in the next 2 days, treatment by a physician is indicated.

Legend: *CPR* Cardiopulmonary resuscitation

**Table 2 Tab2:** Level of care according to “point of care” and corresponding treatment recommendations

Point of care	Name	Recommended action
1	EMS	Medical treatment should be provided by the Emergency Medical Service (EMS).
2	Hospital/ED	Medical treatment should be provided at a hospital in an ED.
3	Physician	Medical treatment should be provided by a registered outpatient care physician.
4	Tele-consultation	The person concerned should be advised in a teleconsultation on how to proceed.

Legend: *ED* Emergency department, *EMS* Emergency medical service

Participants in the multicentre cohort study will be assessed by study personnel using SmED-Contact + and asked to self-assess their symptoms using SmED-Patient. The order of the assessments is randomized. The assessments are conducted using a tablet, with the assessments being processed and stored in a web-based study entity provided by the Central Institute for Statutory Health Insurance in the Federal Republic of Germany (Zi).

An expert panel (blinded to the SmED patient's recommendation) will recommend the level of care for each case, before the expert panel is presented with the SmED patient’s recommendations for the level of care to assess the appropriateness and risk of the recommendation for the patient’s safety (see Table 7). The comparison between SmED-Patient and SmED-Contact +, the latter conducted by a provider, provides additional validation of patient self-assessment with SmED-Patient.

SmED is a Class IIB medical product certified according to the Medical Device Directive (MDD). The study is conducted in accordance with the Declaration of Helsinki and relevant principles of ICH-GCP. ISO 14155 has been considered where applicable (informed consent, data protection, certified training for SmED-Contact + users), though full compliance is not required as SmED is used within its intended use.

### Criteria for discontinuing or modifying allocated interventions {11b}

Study personnel will assess participants’ ability to complete the SmED-Patient assessment and prospective survey prior to study enrollment. If participants have moderate difficulty completing the study measures, they may receive assistance from study personnel (e.g., technical support). In the event of severe difficulty in performing and completing the relevant study measures, study staff will consider the case exclusion from the study.

### Strategies to improve adherence to the interventions {11c}

Not applicable.

### Relevant concomitant are permitted or prohibited during the trial {11d}

Study participants are asked not to use any other symptom checkers during the study period of t0 in the ED.

### Provisions for post-trial care {30}

Not applicable.

### Outcomes {12}

#### Primary outcome

Accuracy, measured as percentage of the perfect agreement in the assessment of the binary level of care between SmED-Patient and the expert panel for patients who self-referred to the ED.

SmED-Patient gives recommendations to the level of care in the following categories (see also Table 2):Emergency Medical Service (EMS),Hospital Emergency Department (ED),Registered outpatient care physician,Teleconsultation.

For the purposes of the study, the categories are combined into two levels, as these reflect the sectoral separation and empirically existing levels of care in Germany:Emergency Care: ED, EMSOutpatient Care: Registered outpatient care physician, teleconsultation (performed by a registered outpatient care physician).

The primary endpoint will be operationalized as a comparison of the level of care recommended by SmED-Patient and the expert panel for each case (see Table 3). Given that directing patients to the most appropriate level of care is the central purpose of algorithms like SmED, the primary endpoint of this study focuses on the perfect agreement between the recommendations of SmED-Patient and the expert panel in terms of binary care level only. The recommended time to treat will be examined as a secondary endpoint, as it is primarily relevant for patients with complaints suitable for outpatient care [10].

**Table 3 Tab3:** Operationalization of the perfect agreement assessment

		**Expert panel**	
		**Emergency care**	**Outpatient care**
**SmED-Patient**	**Emergency care**	**Perfect agreement**	Mismatch
	**Outpatient care**	Mismatch	**Perfect agreement**

Legend: Emergency care = ED, EMS; outpatient care = outpatient care physician, telemedicine

#### Primary null hypothesis

The perfect agreement on the binary care level between SmED-Patient and expert panel is less than or equal to 58.5%.

#### Secondary outcomes

The secondary outcomes are as follows:Symptom assessment overlap and utility: Assessment of recommendation and symptom assessment by SmED-Patient compared to a retrospective physician assessment and the utility of SmED-Patient in the ED (physician assessment in a sub-sample of *n* = 30–60 cases; based on an adapted version of a validated assessment sheet [10]).Agreement of SmED ratings: Percentage of agreement between the recommendations of SmED-Patient and SmED-Contact +.Patient safety and appropriateness: Percentage of cases in which the SmED-Patient recommendation is judged by the experts to be appropriate, appropriate but too cautious, or inappropriate and potentially hazardous (judged according to a range of appropriateness) (see Table 7).Patient assessment of urgency: Percentage of disagreements between patients’ self-assessed urgency and SmED-Patient assessed urgency (see Table 4).Patient utility: Evaluation of utility, including comprehensibility, usability, confidence with responses, response time, satisfaction, trust and hypothetical compliance as well as preparedness for the medical consultation. Subgroup analysis: Investigation of aspects that influence patients’ assessment of SmED-Patient, e.g. health literacy, age.Provider utility: Qualitative evaluation of the utility, including practical utility and perceived benefits of the SmED-Patient short report and of SmED-Patient (full assessment) by ED personnel in focus groups.Feasibility: Qualitative assessment of the feasibility of implementing SmED-Patient in the ED setting.

**Table 4 Tab4:** Overview of target variables and corresponding survey instruments

Target variable	Instrument
Reasons for ED presentation	Measured using an instrument designed by the research group to identify reasons and motives (see Additional file 1)
Patients’ assessment of urgency	Measured using SmED’s categorization of urgency: 1) Emergency (Immediately); 2) As soon as possible; 3) Within 24 h; 4) More than 24 h [13]
Health literacy	HLS19-Q12 (sub-dimension for coping with illness, items 1 to 4) [23], HLS19-COM-P-Q6 (short version) [24]
Sources of information for symptom assessment prior to ED presentation	Measured using an adapted instrument tested within the research group [25]
Medical care received for presented symptom(s) prior to ED presentation	Measured using an adapted instrument tested within the research group [25]
Sociodemographic and socioeconomic baseline data	Validated instruments from established survey panels (e.g., SOEP & ALLBUS) [26, 27]
Patients’ perspective on utility of SmED-Patient in the ED	Measured using the G-MAUQ-S [28], supplemented by dimensions of comprehensibility, confidence with responses, trust and hypothetical compliance as well as preparedness for the medical consultation
Hypothetical compliance with SmED-Patient advice	Prompted with a patient vignette for influenza and advice to seek outpatient care within 24 h, based on [20]
Physicians’ perspective on utility of SmED-Patient in the ED	Measured using an adapted instrument tested within the research group [13]

Legend: *ALLBUS* German General Social Survey, *SOEP* Socio-Economic Panel Germany, *G-MAUQ* German version of the mHealth App Usability Questionnaire, *HLS19-Q12* Instrument to measure General Health Literacy, *HLS19-COM-P-Q6* Instrument to measure Communicative Health Literacy in interaction with physicians, *ED* emergency department

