• Assessment of mobility	• Vital parameters, triage category, lead symptom, overall clinical impression and anamnesis
• Assessment of general condition	
• Assessment of treatment urgency and appropriate care level	

Furthermore, in a sub-group of *n* = 30–60 patients, ED physicians evaluate the utility of SmED-Patient retrospectively. They therefore receive a summary (short report) of the SmED-Patient assessment as well as all routine ED data as well as the further hospital course in case of admitted patients. The ED physicians provide an evaluation of the digital anamnesis and symptom assessment generated by SmED-Patient in terms of completeness and appropriateness of the questions asked. They also assess the utility of the SmED-Patient summary for assessing patients’ complaints and treatment urgency in routine ED care. For this purpose, a separate assessment sheet has been developed. This assessment is conducted subsequent to the patient’s treatment and is based on a comparison of the symptom summary provided by SmED-Patient and the medical routine data. Table 6 outlines the criteria utilized by the physicians in making this assessment, as well as the variables derived from the routine data set.

**Table 6 Tab6:** Attending physician evaluation of the symptom assessment and the utility of the SmED-Patient summary

Assessment sheet	Evaluation basis
• Evaluation of completeness, appropriateness and utility of SmED-Patient symptom assessment summary	• Vital parameters
	• Triage category
	• Leading symptom and medical anamnesis
	• ED diagnostics, diagnoses, treatment as well as data from inpatient stays and discharge data from the ED and hospital
	• SmED-Patient symptom assessment (summary version)

Legend: *ED* emergency department, *SmED* Structured Initial Medical Evaluation Assessment Germany (German: Strukturierte Medizinische Ersteinschätzung Deutschland), *SmED-Patient* Self-Assessment Version of SmED

Finally, routine data from the ED and hospital documentation system are extracted.

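### The first secondary outcome sets SmED-Patient's recommendation against a physician assessment, but the physician procedure as described yields no care level or urgency to compare it with

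*Protocol article*

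**What the plan says.** Under Objectives {7}, the first secondary objective is "To investigate SmED-Patient’s recommendation and symptom assessment compared to the retrospective symptom assessment of attending ED doctors", together with the utility of the short report. Under Outcomes {12}, the matching outcome is the "Assessment of recommendation and symptom assessment by SmED-Patient compared to a retrospective physician assessment". Both place it in a sub-sample of 30–60 cases.

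Module 1 describes how the physician data arise. Of the physicians it says: "They therefore receive a summary (short report) of the SmED-Patient assessment as well as all routine ED data", and for admitted patients the later hospital course as well. They judge the digital history and the "symptom assessment generated by SmED-Patient in terms of completeness and appropriateness of the questions asked". Module 1 adds: "They also assess the utility of the SmED-Patient summary for assessing patients’ complaints and treatment urgency in routine ED care". Table 6 condenses this to a single assessment entry covering the same three qualities of the summary, and it lists the SmED-Patient summary among the materials on which the rating is based.

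**The concern.** According to the Intervention description and Tables 1 and 2, a SmED recommendation has two parts: when to treat and where. To compare a recommendation with a physician's view, the physician must state a care level, a time to treat, or both. The described procedure contains neither. It contains opinions about the summary.

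If the form matches its description, a listed secondary outcome has no data for one of its two parts. Whoever analyses it would have to drop that part without notice or present a rating of the summary as though it were agreement on the recommendation. For the symptom part, the physician judges overlap while looking at the text being judged, which may pull ratings towards agreement.

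**Working it through.** The plan gives no figure for this outcome: the sample-size section covers only the primary endpoint and the focus groups. The check is therefore a side-by-side reading.

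**1. What each rater is described as recording**

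| Rater | Own care level | Own urgency | SmED-Patient output seen before the own rating? |
|---|---|---|---|
| ED nurse (Module 1, Table 5) | yes, per Table 2 | yes, per Table 1 | no; clinical personnel are blinded |
| Expert panel (Module 2) | yes | yes | no; shown only afterwards |
| ED physician, 30–60 cases (Module 1, Table 6) | none described | none described | no own rating described; short report supplied with the record |

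**2. The recommendation part.** Urgency enters the physician task only as something the summary might help to assess. That is a rating of usefulness, not an urgency rating. From what is described, no agreement on care level or time to treat between physician and SmED-Patient can be calculated.

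**3. The symptom part.** Module 1 says that the physician's judgement rests on setting the SmED-Patient summary against the routine medical data. Those data include the leading symptom, history, diagnostics and diagnoses. Module 1 also says that clinical personnel are blinded to both SmED results. A reference recorded without sight of those results therefore exists, and the comparison can be made. What is not blinded is the judgement of overlap, and no first step without the short report is described.

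**4. What the repaired outcome could show.** If the items are added, agreement would be reported as x/n with an exact 95% interval, where lower = Beta quantile(0.025; x, n−x+1) and upper = Beta quantile(0.975; x+1, n−x). The protocol states no expected physician agreement. As assumptions I take 70%, borrowed from the primary endpoint, and 50% for range:

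- n = 30, x = 21 (70%): 50.6% to 85.3%
- n = 60, x = 42 (70%): 56.8% to 81.2%
- n = 30, x = 15 (50%): 31.3% to 68.7%
- n = 60, x = 30 (50%): 36.8% to 63.2%

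These intervals are wide but usable for a descriptive secondary outcome.

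**The case against.** The best defence has four parts.

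First, the objective describes the comparator as the SmED output "compared to the retrospective symptom assessment of attending ED doctors", so a physician care level was perhaps never intended. The outcome can also be read as the physician appraising what SmED produced. This is fair. It narrows the conflict to the word *recommendation*, but that word stands in both places and nothing described serves it.

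Second, the form is not shown and Table 6 is only an outline. Its origin is also described in different ways: adapted from one cited source under Secondary outcomes, from another in Table 4 for physician-rated utility, and as a separately developed sheet in Module 1. Further items cannot be excluded. This stands, and the conclusion must be limited to the procedure as described. Condensation alone is a weak explanation, though, because the parallel Table 5 does name urgency and care level for nurses.

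Third, physicians already rate care level and treatment time for every valid case in Module 2, blinded first. This is true and it limits the consequences. But those are the expert panel, not the ED physicians named in this outcome.

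Fourth, completeness cannot be judged without seeing both the summary and the record, and the protocol openly calls the assessment retrospective. This stands as well. Hindsight in the utility rating is a declared feature of the design. Restricting the physician to triage data would not reliably remove it for someone who had treated the patient.

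**Conclusion.** The point holds in a limited form. As described, the recommendation part of the first secondary outcome has no physician counterpart in any of the 30–60 sub-sample cases. The symptom part is feasible, but it is judged with the short report in view and is open to anchoring.

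A reader might infer that the whole comparison is impossible, that there is no independent record to compare with, or that the number of analysable pairs is known to be zero. The documents do not support any of these. Module 1 specifies a symptom comparison, its reference comes from clinical staff blinded to the SmED results, and the full content of the form is not shown.

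The primary endpoint is untouched, because its comparator is the expert panel, which rates before seeing SmED-Patient. The conclusion assumes that Module 1 and Table 6 describe the physician sheet completely in this respect. If the sheet already carries care-level and urgency items, what remains is to say so and to state whether they are completed before the short report is seen.

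**What to change.** Add to the physician sheet the care-level (Table 2) and time-to-treat (Table 1) items already used on the nurse sheet. Have them completed from the routine data and locked in REDCap before the short report opens. The existing ratings of the summary then follow unchanged. Report physician–SmED-Patient agreement from the locked items, with an interval, and describe it as retrospective.

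The cost is a few existing items and a fixed page order on one form for 30–60 cases, with slightly more physician time per case and no extra staff. The physician will still know the clinical course, and this change does not claim to alter that.

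If the added rating is not wanted, delete *recommendation* from the first secondary objective and outcome, and report what remains as an unblinded, retrospective physician rating of the symptom summary. That is a wording change only, but it gives up the comparison.
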